### Methods of participant identification

The UK-EDI Study will establish a nationwide cohort representative of the UK population with recruitment occurring across primary and secondary care settings, including specialist diabetes centres and primary care hubs. In an internal pilot study, we established pathways for identification of individuals with NOD from primary care, with recruitment in secondary care.^24^ In the UK-EDI study, participants will either be identified in primary care sites and recruited in the primary care setting or identified in primary care sites and recruited in a local secondary care recruiting hub. The use of electronic health records will facilitate 6 monthly identification of suitable participants in each setting. Participants may present directly to secondary care services as emergency presentations of NOD and those individuals will be recruited in secondary care. Participants may also be identified from specialist inpatient teams such as diabetes and endocrinology, hepatobiliary and pancreatic surgery, and gastroenterology. The screening framework is flexible to account for local organisation of services across the UK (figure 2).

**Figure 2 F2:**
[figure not shown]
Schematic of UK-EDI study recruitment and participant follow-up. EMIS, Egton Medical Information Systems (electronic healthcare record system); HbA1c, glycated haemoglobin; UK-EDI, UK Early Detection Initiative for Pancreatic Cancer.

### Study timeline

Eligible individuals will be provided with a participant information sheet explaining the UK-EDI Study and will be given an opportunity to ask questions prior to signing an informed consent form. At the baseline visit, a full medical, drug and surgical history will be elicited, including demographic, social and anthropometric data. Participants will also be asked about a range of symptoms over the preceding 6–12-month period, which may indicate early signs of PDAC. Participants will be asked specifically about weight changes, including in the context of a weight management programme. Quality of life assessment will be via a health-related Quality of Life Questionnaire (EuroQol Research Foundation: EQ-5D-5L),^25^ and diabetes management will be captured via a Diabetes Self-Management Questionnaire (DSMQ).^26^ The DMSQ is an instrument which assesses diabetes self-care activities associated with glycaemic control. Blood samples will be taken for measurement of haemoglobin A1c (HbA1c) and research plasma and serum samples will be taken for biobanking according to GCP Laboratory standards to allow for translational research. Sites may also provide the results of other haematological and biochemical blood results including full blood count, liver function tests, urea and electrolytes, and lipid profiles, if these are being taken for routine diabetes care. Supplemental blood test results are not required for all participants.

Follow-up visits will be at 6, 12, 18 and 24 months after the baseline visit. Quality of Life, DSMQ and case report form data will be collected at baseline and each follow-up visit. At 36 months, there will be a search of NHS Digital to determine the number of events of PDAC diagnosis in the enrolled cohort.

Key clinical and translational characteristics, including timeframes, of the UK-EDI cohort are listed in table 2.

**Table 2 T2:** Eligibility criteria and relevant definitions of the UK-EDI cohort

Data item	Details
EDTA stored blood	Translational blood samples taken at baseline, 6, 12, 18 and 24 months stored to GCP standards
Serum stored blood	Translational blood samples taken at baseline, 6, 12, 18 and 24 months stored to GCP standards
HbA1c measurements	HbA1c measurements from diagnosis, baseline, 6, 12, 18 and 24 months
Demographics	Details including ethnicity, smoking, and alcohol status
Anthropometric data	Height, weight, waist and hip measurements taken at baseline, 6, 12, 18 and 24 months
Biochemistry and symptomology of diabetes onset	Details regarding symptoms at the time of diabetes diagnosis and prior biochemical (HbA1c) data pre-diagnosis (left-window)
Symptomology relevant to pancreatic cancer	Detailed information regarding symptoms typical of onset of pancreatic cancer, and changes from baseline at 6, 12, 18 and 24 months
DSMQ	The diabetes self-management questionnaire. A validated instrument assessing self-care behaviours associated with diabetes control. Measured at baseline, 6, 12, 18 and 24 months
EQ-5D-5L	Standardised measure of health-related quality of life measured at baseline, 6, 12, 18 and 24 months
Medical and surgical history	Changes to medical and surgical diagnoses at baseline, 6, 12, 18 and 24 months
Medication history	Changes to prescribed medication, including for diabetes, at baseline, 6, 12, 18 and 24 months
Pancreatic malignancy data	Data from subsequent pancreatic cancer diagnoses, including surgical and oncological therapy.

DSMQ, Diabetes Self-Management Questionnaire; EQ-5D-5L, EuroQol Research Foundation Quality of Life Questionnaire; GCP, good clinical practice; HbA1c, glycated haemoglobin.

### Objectives

#### Primary

The primary objective is to recruit individuals to a bespoke standardised cohort of individuals aged 50 years or older with NOD (HbA1C ≥48 mmol/mol, (6.5%)) and no prior history of DM, ensuring the standardised collection and biobanking of samples while acquiring the molecular, epidemiological and demographic factors in order to advance the early detection of PDAC.

#### Secondary

The secondary objectives are to validate carbohydrate antigen 19-9 (CA19-9) and other novel markers already identified with potential to distinguish T3cDM (including PDAC related) from T2DM and to establish the economic impact of diagnosing PDAC early in individuals with NOD.

#### Exploratory

The opportunistic and exploratory objectives are to study molecular, epidemiological and demographic factors to further stratify risk of PDAC and to use the UK-EDI cohort for biomarker discovery.

### Statistical methodology

#### Sample size

We aim to recruit 2500 patients with NOD aged 50 years and older, with a follow-up of 36 months. The target size of 2500 is pragmatic, based on costs and what is practically possible. It is anticipated that 0.8%–1% of the group will receive a diagnosis of PDAC in the 3-year follow-up time period.^15^

Thus, the UK-EDI cohort is expected to yield approximately 21–25 PDAC diagnoses (or 17–20 cases with 20% attrition). This study will provide data on the incidence of PDAC in individuals with NOD in the UK and will serve as the benchmark/reference point for future work.

Formal power calculations to determine associations between clinical/biological subgroups and the diagnosis of PDAC are difficult as it is not yet known what fraction of any subgroups will split the available patient population.

The UK-EDI cohort will contribute to larger international efforts aimed at determining the feasibility of detecting resectable PDAC in individuals over 50 years of age who are newly diagnosed with diabetes mellitus.^23^

#### Data analysis plan

The primary endpoint of interest is clinically diagnosed PDAC within 3 years of a new diagnosis of DM. The measurement of clinical characteristics, including glucose control (HbA1c) along with biological and epidemiological measures at five time points over the course of the cohort study, will help inform the incidence of PDAC in individuals with NOD in the UK.

Analysis of PDAC diagnosis will be performed using longitudinal methods, assessing the effect of biological and epidemiological markers while adjusting for relevant clinical characteristics.

Validation of biomarkers will include receiver operator characteristic curve analysis to determine biomarker performance characteristics. Further exploratory analysis will be carried out using multivariate techniques such as principal component and hierarchical cluster analyses in order to reduce the dimensionality of the data and identify naturally forming groups within the data, respectively.

Secondary analyses will focus on the time to detection of PDAC using a time-to-event approach. The probability of detecting PDAC will be calculated across subgroups using the method of Kaplan-Meier. Inclusion of biological and clinical characteristics will be incorporated using joint survival/longitudinal modelling techniques. Detailed information including clinical, epidemiological and biomarker data will be used to build a PDAC risk score, or validate emerging risk scores.

To assess the cost-effectiveness of early diagnosis of PDAC in individuals with NOD, the clinical pathway will be mapped and a literature review conducted to ensure that the model is populated with relevant current data. The study questionnaires will be used to update and calibrate models with data pertaining to PDAC cases versus controls. At the cohort level, a Markov model will be constructed to incorporate assumptions about what would happen to individuals if they were identified earlier. In addition, a discrete event simulation model will be developed to capture stochastic variations at the level of each individual. The impact of early diagnosis will be analysed using the updated Markov and simulation models. With respect to individuals detected earlier in a future screening protocol implemented in NOD, a key uncertainty is the stage of disease that would be diagnosed. A probabilistic sensitivity analysis, informed by the literature, will be conducted on a range of scenarios, including epidemiological, clinical and biomarker data.

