### Eligibility criteria

Eligibility criteria and relevant definitions of the UK-EDI cohort are provided in table 1.

**Table 1 T1:** Eligibility criteria and relevant definitions of the UK-EDI cohort

Criteria/definition	Details
Inclusion criteria	Aged≥50 years at the time of study entry New-onset diabetes (defined at HbA1c≥48 mmol/mol (6.5%) diagnosed within 6 months of study entry Willing to provide written informed consent prior to performing any protocol-related procedures Willing and able to comply with the protocol for the duration of the study, including scheduled follow-up visits
Exclusion criteria	Diagnosis or treatment of pancreatic cancer, peri-pancreatic cancer, or pancreatic endocrine cancer Previous surgical resection of the pancreas Diagnosis of diabetes>6 months prior to study entry Pregnancy Condition preventing study investigation and follow-up Inability or incapacity to give written informed consent
Definition of new-onset diabetes	HbA1c≥48 mmol/mol (6.5%) diagnosed within 6 months of study entry
Identification of PDAC diagnoses	NHS digital will be interrogated to update occurrence of PDAC

HbA1c, glycated haemoglobin; PDAC, pancreatic ductal adenocarcinoma; UK-EDI, UK Early Detection Initiative for Pancreatic Cancer.

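### The primary endpoint is counted from diabetes diagnosis, but people enter up to 6 months later and free of diagnosed pancreatic cancer; the time origin needs to be stated once and late entry allowed for

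*Protocol article*

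**What the plan says.** All references are to the protocol article.

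- **Endpoint** (Data analysis plan): "The primary endpoint of interest is clinically diagnosed PDAC within 3 years of a new diagnosis of DM". The clock starts at diabetes diagnosis.
- **Entry** (Eligibility criteria, Table 1): new-onset diabetes is "HbA1c≥48 mmol/mol (6.5%) diagnosed within 6 months of study entry". The first exclusion criterion is "Diagnosis or treatment of pancreatic cancer, peri-pancreatic cancer, or pancreatic endocrine cancer".
- **Finding participants** (Methods of participant identification): electronic records are used to "facilitate 6 monthly identification of suitable participants in each setting", so a gap of some months between diagnosis and entry is to be expected.
- **Follow-up** (Study timeline): "Follow-up visits will be at 6, 12, 18 and 24 months after the baseline visit". The same paragraph goes on: "At 36 months, there will be a search of NHS Digital to determine the number of events of PDAC diagnosis". The origin of those 36 months is not given; baseline is the natural reading.
- **Yield** (Sample size): "It is anticipated that 0.8%–1% of the group will receive a diagnosis of PDAC in the 3-year follow-up time period". From this the article expects 21–25 diagnoses among 2500 people, or 17–20 with 20% attrition. It also says the study will supply UK incidence data as a reference for later work.
- **Time-to-event analysis** (Data analysis plan): "Secondary analyses will focus on the time to detection of PDAC using a time-to-event approach". Kaplan-Meier and joint models are named, without a time origin or an entry time.

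**The concern.** The endpoint uses one clock. The visits, and apparently the final search and the yield, use another. The two origins differ by up to 6 months, and the gap is not neutral. Everyone enrolled has by definition passed through it without a pancreatic cancer diagnosis. If those months count as time at risk from diabetes diagnosis, the estimate includes time in which no event could occur. This is left truncation.

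At the other end, a search at 36 months from baseline reaches 36–42 months after diabetes diagnosis. The number of events it returns would then differ from the endpoint in two ways: it lacks the pre-entry cases, and it includes some cases beyond 3 years.

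At stake is the incidence figure that the study offers as a UK reference. The Introduction describes diabetes in this setting as a manifestation of the cancer itself. It is therefore plausible, though it is an inference, that diagnoses cluster soon after diabetes diagnosis, in the window that is lost. Such an error does not shrink when cohorts are pooled, and it would spoil comparison with studies that count from diabetes diagnosis.

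**Working it through.** **1. The plan's own yield.** Events = N × risk. 2500 × 0.8% = 20 and 2500 × 1% = 25; with 20% attrition, 20 × 0.8 = 16 and 25 × 0.8 = 20. The article gives 21–25 and 17–20. Its lower limit corresponds to 21/2500 = 0.84%, and 21 × 0.8 = 16.8. The figures are reproduced closely as N × risk, with no term for late entry.

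**2. Share of 3-year cases diagnosed before entry.** Assumptions that are not in the documents: entry lag t is uniform over 0–6 months, and the share of 36-month cases diagnosed by month t is (t/36)^k. Here k = 1 is a constant hazard and k < 1 is front-loaded. The mean share lost is

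L(k) = (1/6)∫₀⁶ (t/36)^k dt = (1/6)^k / (k + 1).

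| k | (1/6)^k | L(k) | 3-year incidence without delayed entry, if the true value is 1.0% |
|---|---|---|---|
| 1 | 0.167 | 0.167/2 = 8.3% | 0.92% |
| 0.7 | 0.285 | 0.285/1.7 = 16.8% | 0.83% |
| 0.5 | 0.408 | 0.408/1.5 = 27.2% | 0.73% |

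If everyone entered at exactly 6 months, the loss would be (1/6)^k itself: 17%, 29% and 41%.

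**3. Check by simulation.** The true 3-year risk was 1.0%, with uniform entry. The share of 3-year cases falling in the first 6 months was set to 1/6, 30% or 50%.

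| Share in first 6 months | Without delayed entry | Left-truncated Kaplan-Meier |
|---|---|---|
| 1/6 (constant hazard) | 0.92% | 1.00% |
| 30% | 0.82% | 0.99% |
| 50% | 0.65% | 0.95% |

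Delayed entry recovers most or all of the shortfall.

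**4. Effect on case numbers, under each clock.** Suppose that 0.8%–1% is a 36-month risk from diabetes diagnosis, which the article does not say. Counting only to 36 months after diabetes diagnosis leaves 20 × (1 − L) to 25 × (1 − L) cases. Counting to 36 months after baseline adds the late cases G(k) = 6[(7/6)^(k+1) − 1]/(k + 1) − 1, which is 8.3%, 5.7% and 4.1% for the three shapes.

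| k | Cases to 36 months after diabetes diagnosis | Net loss L − G, 36 months from baseline | Cases, 36 months from baseline |
|---|---|---|---|
| 1 | 18.3–22.9 | 0% | 20.0–25.0 |
| 0.7 | 16.6–20.8 | 11% | 17.8–22.2 |
| 0.5 | 14.6–18.2 | 23% | 15.4–19.2 |

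**5. Scale against sampling error.** With 25 cases in 2500, the exact 95% interval is 0.65%–1.47%, that is −35% to +47% around 1.0%.

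**The case against.** The strongest reply is that the article specifies no naive analysis. It names Kaplan-Meier and joint models and leaves the risk sets open. Handling of delayed entry is ordinary SAP content, and neither the SAP nor the full protocol is shown. This stands against anyone who infers that the plan ignores late entry or that its incidence will be biased: the bias is conditional on the method used. It does not remove the conflict between the stated endpoint and the stated schedule, which is in the printed text.

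A reader might also infer that the expected yield is overstated. The documents do not support that. The Sample size section applies 0.8%–1% to the enrolled group over its follow-up, and the time origin of the cited source is not given. If cases are counted for 36 months from baseline, a constant hazard gives no loss at all. Recruitment through emergency presentations and hepatobiliary and pancreatic surgery teams could also raise case numbers, so the net direction of any error is unknown.

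Third, risk from enrolment among people without diagnosed PDAC is a valid quantity and suits a study of occult cancer. This stands, but it is not the endpoint as written.

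Last, an 8% bias is small against the sampling error, and the choice can still be made at analysis because diabetes diagnosis must be dated for eligibility. Both points stand and limit the severity.

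**Conclusion.** The conflict is real: the endpoint starts at diabetes diagnosis, while people are observed from an entry up to 6 months later and only if free of diagnosed pancreatic cancer. If the endpoint is computed as written among enrolled people without delayed entry, the 3-year incidence is too low by about 8% (constant hazard), 17% or 27% (assumed Weibull shapes 0.7 and 0.5), with entry uniform over 0–6 months. No document gives the early timing of diagnoses or the distribution of entry lags, so these figures show a range and are not estimates. The lower end is minor beside sampling error; the front-loaded cases matter for a reference figure.

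That the 36-month search runs from baseline is an inference from its place in the text. That the yield is wrong is not shown. It would also go too far to say that the time-to-event analysis must become primary; the time origin can be settled without that. This is a should-fix point: it affects how the main incidence figure is defined and read, but nothing in data collection is lost.

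**What to change.** State one time origin for the endpoint, the 36-month search and the expected yield, by one of two routes.

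1. **Origin at diabetes diagnosis.** Estimate incidence with left-truncated risk sets: each person enters at the baseline visit, and cases count to 36 months after diabetes diagnosis. Interpret the curve only from the time at which the risk set is adequate, because few people are under observation in the first weeks. A search at 36 months from baseline covers this window for everyone, provided it returns the date of each PDAC diagnosis and not only a count.
2. **Origin at enrolment.** Redefine the endpoint as 3-year risk from enrolment among people free of diagnosed PDAC, and label it so wherever it is reported.

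In either case, say which clock the 0.8%–1% refers to. Restate the 21–25 yield only if that risk is counted from diabetes diagnosis.

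The cost is wording in the protocol or SAP and one start-time variable, using a date already needed for eligibility. Under the first route, the delayed-entry method also assumes that time of entry is unrelated to the hazard of PDAC diagnosis. Recruitment through pancreatic surgery teams may strain that assumption, so a sensitivity analysis without those recruits is sensible.

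### Kaplan-Meier is named for the subgroup probability of PDAC detection; if deaths are censored, it slightly overstates the chance of being diagnosed, more so where mortality is higher

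*Protocol article*

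**What the plan says.** The endpoint is an absolute event over a fixed horizon (Data analysis plan): "The primary endpoint of interest is clinically diagnosed PDAC within 3 years of a new diagnosis of DM". The time-to-event work is secondary: "Secondary analyses will focus on the time to detection of PDAC using a time-to-event approach". The estimator is then named: "The probability of detecting PDAC will be calculated across subgroups using the method of Kaplan-Meier". Biological and clinical characteristics are to enter through joint survival/longitudinal models.

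Under Sample size the article gives the cohort and horizon: "We aim to recruit 2500 patients with NOD aged 50 years and older, with a follow-up of 36 months". It also gives the expected risk: "It is anticipated that 0.8%–1% of the group will receive a diagnosis of PDAC in the 3-year follow-up time period". It adds that the study's incidence data "will serve as the benchmark/reference point for future work".

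Under Study timeline, ascertainment at the end of follow-up is described as follows: "At 36 months, there will be a search of NHS Digital to determine the number of events of PDAC diagnosis in the enrolled cohort". The article does not mention competing risks, cumulative incidence or the handling of death. Table 1 sets no upper age limit and no life-expectancy criterion, although it excludes people whose condition would prevent investigation or follow-up.

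**The concern.** Death without PDAC is a competing event, because it makes later detection impossible. Kaplan-Meier with deaths censored treats the dead as if they could still be diagnosed at the same rate as survivors. One minus Kaplan-Meier then describes a hypothetical population in which nobody dies of anything else. The quantity in the endpoint and in the Sample size section is different: the share of real participants who receive a diagnosis within 3 years.

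The gap depends on mortality, so it is not the same in every subgroup. Two subgroups with the same rate of PDAC diagnosis among the living, but different mortality, would have similar Kaplan-Meier probabilities and different true probabilities of diagnosis. Recruiting more people reduces random error but not this bias.

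**Working it through.** **Inputs from the article.** N = 2500; 3-year PDAC risk 0.8% to 1%; horizon 36 months; 20% attrition.

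**Assumed inputs.** Three-year probability of death without PDAC, M, from 5% to 40%, because the article gives no mortality figure. It does not say whether its 20% attrition includes deaths, so that figure cannot stand in for M. Both hazards are taken as constant.

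**The plan's own event count.** 2500 × 0.8% = 20 and 2500 × 1% = 25; after 20% attrition, 16 and 20. The article gives 21–25 and 17–20. The upper ends agree and the lower ends differ by one; a risk of 0.85% gives 21.25 and 17.0. The difference has no bearing on this point.

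**Formulas.** With cause-specific hazards h1 (PDAC) and h2 (death without PDAC) per year:

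- One minus Kaplan-Meier, deaths censored: 1 − exp(−3·h1)
- Cumulative incidence: h1/(h1 + h2) × [1 − exp(−3·(h1 + h2))]
- h1 = −ln(1 − 0.01)/3 and h2 = −ln(1 − M)/3

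**Worked case, M = 25%.** 3·h1 = 0.01005 and 3·h2 = 0.28768, sum 0.29773. Cumulative incidence = (0.01005/0.29773) × (1 − 0.99 × 0.75) = 0.03376 × 0.2575 = 0.869%. Kaplan-Meier gives 1.00%, so the excess is 0.13 points, and 1.00/0.869 = 1.15.

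**Results when one minus Kaplan-Meier is 1.00%**

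| Assumed M | Cumulative incidence | Excess (points) | Relative excess |
|---|---|---|---|
| 5% | 0.975% | 0.03 | 2.6% |
| 10% | 0.949% | 0.05 | 5.4% |
| 20% | 0.897% | 0.10 | 11.6% |
| 25% | 0.869% | 0.13 | 15% |
| 40% | 0.783% | 0.22 | 27.7% |

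At a 0.8% risk and M = 10%, the cumulative incidence is 0.759%, an excess of 0.04 points and the same relative excess of 5.4%. The relative bias therefore depends on mortality and hardly at all on the PDAC risk.

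**Short-form check.** For a rare event the ratio of cumulative incidence to one minus Kaplan-Meier is close to M/m with m = −ln(1 − M): 0.05/0.0513 = 0.975; 0.10/0.1054 = 0.949; 0.25/0.2877 = 0.869. These agree with the table.

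**Against sampling error.** The standard error of a 1% risk is √(0.01 × 0.99/2500) = 0.20 points in the whole cohort, and √(0.01 × 0.99/500) = 0.44 points in an assumed subgroup of 500.

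**Against the error of a comparison.** Take two subgroups with M = 5% and M = 25% and an assumed 10 events each. The distortion of the log risk ratio is ln(1.151/1.026) = 0.115, against a standard error of about √(1/10 + 1/10) = 0.45.

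**The case against.** The strongest reply is that the bias is too small to matter here. With about 17 to 25 events in all, it is well inside the sampling error of any subgroup estimate, the analysis is secondary, and Table 1 keeps out some of the frailest people. This stands, and it sets the weight of the point. It does not make the named estimator the right one for an absolute probability.

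A second reply is that this is a condensed article, and that censoring rules and linkage fields belong in the full protocol or analysis plan. That stands for those details. A reader might infer from the Study timeline sentence that deaths will not be obtained; the article does not show that, and its silence is no fault. The choice of Kaplan-Meier, however, is stated.

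Three further inferences are tempting but not supported:

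- **That uncaptured deaths would bias the result in the opposite direction.** They would not, for the probability of diagnosis. If everyone stays in the risk set to a common 36-month search and there is no other censoring, one minus Kaplan-Meier is simply the proportion diagnosed, which is the cumulative incidence.
- **That age or comorbidity subgroups are the ones affected.** The article names no subgroups for this analysis; under Sample size it speaks only of clinical and biological ones. Groups with similar mortality would be little distorted relative to each other.
- **That these estimates feed the cost-effectiveness model.** The article bases that model on a literature review, the study questionnaires and a literature-informed sensitivity analysis. It does not say that Kaplan-Meier estimates enter it, nor that they enter the risk score.

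**Conclusion.** The point holds as a conditional one. If deaths without PDAC are censored, the stated method overstates the probability of being diagnosed, and by more where mortality is higher. It would go too far to say outright that the subgroup probabilities will be overstated, because the article does not give the censoring rule.

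The size rests on assumed mortality and constant hazards. At 5% to 10% mortality, a range assumed for the cohort as a whole, the excess is 0.03 to 0.05 points on a 1% risk, about a quarter of the 0.20-point standard error or less. At 25% it is 0.13 points, still below the 0.44-point standard error of an assumed subgroup of 500. It is a minor systematic bias in a secondary analysis, unlikely to change a subgroup conclusion. It is worth correcting because the correction is standard and the study offers its incidence data as a reference for others.

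**What to change.** In the Data analysis plan, replace Kaplan-Meier for the subgroup probabilities with the Aalen-Johansen cumulative incidence of PDAC diagnosis, with death without PDAC as the competing event. State how deaths are handled.

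Make sure that dates of death and of PDAC diagnosis both come with the planned NHS Digital search. Keep cause-specific hazard or joint models for associations, where censoring deaths is valid. Any absolute risk derived from them, for example in a risk score, should also account for death.

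The cost is a line or two of analysis wording, at most one extra linkage field, and slightly lower reported probabilities.
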